### Study procedures

Before data collection, local assessors and research assistants are selected and trained in the data collection procedures by the core research team in a one-week workshop. In addition to prior experience in research projects on social and health-related topics, the assessors are required to hold a university bachelor’s degree, be fluent in Urdu, which is the national language and the main mode of teaching across the country, as well as in the local language, and have basic level fluency in English. The assessors are blind to the allocation of the schools to the intervention and control groups. The assessment of students consists of a structured interview and a cognitive test, which take about one and a half hours in total. The assessment of teachers consists of a structured interview and takes about one hour. In the interview, assessors directly enter participants’ responses into Android tablets using the survey software SurveyToGo [53]. The cognitive testing is also administered to the students on the tablets using Inquisit Web [54]. All measures are administered with standardized introduction and administration procedures to ensure high objectivity and reliability during data assessment. All interview measures have been translated from English to Urdu according to recommended scientific guidelines including blind back-translation [55]. All interviews are conducted in Urdu to ensure participants’ full understanding. Recruitment of local bilingual assessors ensures that no information is lost in translation.

Prior to data collection, selected students receive a letter explaining the study aims and procedures together with an informed consent form for their parents to seek parental consent. Students whose parents have signed the informed consent form are invited to an interview in a quiet and discreet setting in the school premises. Before the interview, each student is given detailed written and oral information on the study procedure, the confidentiality of their data, and their right to withdraw from the study at any time without any consequences, and they are asked to provide their written consent to participation. Similarly, after being introduced to the study in a formal information session, all teachers at each selected school are invited to participate in an interview, and willing teachers receive detailed written and oral information on the study procedure, the confidentiality of their data, and their right to withdraw from the study at any time without any consequences, and provide written informed consent. The assessment procedures are repeated in the same way at 6-months and 18-months follow-ups. Students can be considered masked throughout the study as the intervention only targets teachers. Given the nature of the intervention, teachers are masked at baseline assessment but unmasked at the follow-up assessments.

#### Intervention description

The ICC-T intervention consists of a 5-day training workshop for teachers that is delivered by local facilitators and focuses on providing teachers with practical information and tools to prevent the use of violent disciplinary strategies in class and improve their interaction competencies with children. Sessions are divided into 5 modules: 1) Sessions about teacher-student interactions aim to promote teachers’ empathy and understanding of their students’ behavior and to raise teachers’ awareness of being a role model for students. 2) Sessions on maltreatment prevention aim to raise teachers’ awareness of the negative consequences of violent discipline on children’s well-being by inviting teachers to reflect on their own experiences of violence as a child and connect these experiences and associated feelings to the causes and consequences of their current violent behavior. 3) Sessions on effective discipline strategies aim to equip teachers with non-violent behavioral skills and tools helping them to maintain and reinforce desired behaviors and to change undesirable behavior by students. 4) Sessions on identifying and supporting burdened students intend to raise teachers’ awareness for common internalizing and externalizing problems among students and to increase their ability to identify and adequately support students with these problems. 5) Lastly, sessions on implementation aim at integrating the learned knowledge and skills into everyday school life and at ensuring sustainability to establishing support networks such as peer consultation and collaboration with school counselors (where available) and parents [56].

With behavior change as the primary objective, the content of ICC-T as an intervention was developed based on attachment theory, behavior modification theory, and social learning theory, and the central aspects of non-violent interaction between teachers and students being based on the work of the Democratic Classroom [57]^.^ For the implementation of the content, established methods that have been shown to lead to a change in behavior, such as inputs, role plays, discussion, and reflections, are used [56]. The structure of the training is important as it allows for a dynamic wherein a willingness to change is initially achieved, which is then followed by practical alternative strategies. Over the course of the week, an atmosphere develops in which curiosity, willingness to change, competence to act, and readiness to act (through motivation and social cohesion) catalyze each other.

#### Intervention procedures

The school-based ICC-T intervention is delivered by facilitators with a background in psychology and/or teaching who have participated in a two-week training including a pilot ICC-T workshop. Participation in the training workshop is free of charge. All teachers at a selected school receive detailed written information on the training procedure, the voluntary nature of their participation as well as their right to withdraw from the training at any point. Teachers who agree to participate in the training need to sign an additional informed consent form. In order to ensure that lessons can continue, half of the teachers in a school receive the intervention in one week and the other half of the teachers in the following week. Confidentiality of participants’ personal data and information shared during the training is ensured at any time. Treatment fidelity is assessed through questionnaires answered by the facilitators and randomly selected participants on each day of the workshop and through video recordings of pre-determined sequences of selected sessions. Questionnaires for facilitators cover information on each session’s duration, applied methods, deviations from the intervention manual and didactical aspects, as well as perceived uptake of the session content by participants. Questionnaires for participants focus on their perceived understanding of the day’s training content and the helpfulness of the applied methods in delivering the content. In addition, all participants evaluate the training contents and methods using a questionnaire at the end of the workshop. Video recordings are evaluated by independent raters to determine whether intervention workshops have been implemented in line with the manual. Contamination is assessed by interviewing the head teacher and five randomly selected teachers at each school around each follow-up timepoint about whether they shared materials or content from the ICC-T intervention with teachers in other schools.

#### Control condition

No intervention is implemented in control schools. The research team is in close contact with the control schools to closely document any similar intervention that takes place at the schools during the study. Apart from the intervention, all data collection procedures at baseline and follow-up assessments are implemented in control schools in the same way as in intervention schools. Similar to intervention schools, the head teacher and five randomly selected teachers at each school are interviewed around the follow-up timepoints about whether they had been in contact with teachers from other schools regarding student discipline.

### Outcomes

Primary, secondary and other outcomes are described below. All outcomes are assessed at all three assessment phases. The selection of assessment instruments considered both the psychometric quality and frequent use in comparable studies. The feasibility study of ICC-T in Pakistan demonstrated the applicability of the instruments in the context of Pakistan and no adaptations were made. Descriptive analyses will be used to examine basic psychometric properties of the measures in the present sample (see section Data analyses). The instruments are translated from English to Urdu using blind back-translation according to scientific standards [55].

#### Primary outcomes

##### Exposure to violence by teachers

Teachers’ use of physical and emotional violence against students in the past week is assessed using the Teacher–Child Conflict Tactics Scale (CTSTC), an adapted version of the Parent–Child Conflict Tactics Scale (CTSPC; [58]). The CTSTC is answered both by students as victims and by teachers as perpetrators of violence. It includes 16 items on experienced physical violence, seven items on experienced emotional violence and three items on witnessed violence by teachers, which are answered on a 6-point Likert scale from 0 (this has never happened) to 5 (more than 10 times). The items on experienced physical and emotional violence are combined to a total sum score as well as subscale scores. The CTS has been used in previous and ongoing trials of ICC-T and has demonstrated acceptable psychometric properties [37, 44, 45, 47, 52]. The CTSPC has been used in a national survey of violence against children in the home setting in Pakistan [59].

#### Secondary outcomes

##### Teachers’ attitudes towards violent discipline

An adapted version of the CTSTC serves as a measure of teachers’ favourable attitudes towards the use of physical and emotional violent discipline. Using the same 23 items as the CTSTC, teachers indicate to which extent they approve the respective act of violent discipline on a 4-point Likert scale from 0 (never OK) to 3 (always or almost always OK). The items are then summed up to a total score of attitudes towards violent discipline (range 0–69), with higher scores indicating more favourable attitudes. The scale has been used to assess teachers’ self-reported attitudes towards violent discipline in previous and ongoing trials of ICC-T [37, 44, 45, 47, 52].

##### Mental health problems

The 35-item version of the Pediatric Symptom Checklist – Youth Report (PSC-Y; [60]) is used to assess students’ emotional and behavioral problems in the past month. The items are rated on a 3-point Likert scale from 0 (*never*) to 2 (*often*) and summed up to a total score of emotional and behavioral problems (range 0–70). The PSC-Y has demonstrated good psychometric properties in a variety of cultural settings [61–63] and is being used in ongoing trials of ICC-T [37, 47]. The Urdu version of the PSC-Y has shown good reliability and validity at identifying adolescents with emotional and behavioral problems in public schools in Rawalpindi district [64].

##### Quality of life

The KIDSCREEN-10 [65] is used as a measure of children’s perceived quality of life. The 10 items cover physical, emotional, social, and behavioral aspects of well-being and functioning and are answered referring to the past week on a 5-point Likert scale ranging from 0 (*not at all)* to 5 (*extremely*). The KIDSCREEN-10 has demonstrated good psychometric quality in assessing children and adolescents’ self-reported quality of life in various cultural settings [65].

##### Cognitive functioning

Five tasks from the tablet application Inquisit are used to assess children’s cognitive abilities including selective attention (Letter Cancellation Task), working memory (Corsi Block Tapping Backwards), response inhibition (Arrow Flanker Task), planning and problem solving (Tower of London) and cognitive flexibility (Wisconsin Card Sorting Test).

#### Other outcomes

##### Academic performance

Students’ grades in core subjects (e.g. Mathematics, English, Science) in the last exams preceding the assessment are requested from the schools’ administrators and compared to exam results taken after the intervention.

##### Peer violence

The 24-item version of the Multidimensional Peer Victimization Scale [MPVS-24; 66] is used to assess children’s experiences of violence by peers in the past month. The MPVS-24 considers the six subtypes of physical victimization, verbal victimization, social manipulation, attacks on property, electronic victimization and social rebuff with four items each. The items are rated on a 3-point scale from 0 (not at all) to 2 (more than once) and combined into a sum score. The original 16-item and the 24-item version of the MPVS have shown good psychometric quality [66]. In addition, sexual violence by peers is assessed using four items from the adolescent version of the Sexual Experiences Survey [67] with the same response scale as the MPVS-24. A study with adolescents in Rawalpindi district found evidence of the reliability and validity of the 16-item version of the MPVS in the context of Pakistan [68].

### Efforts to reduce bias

The following efforts are expected to minimize the risk of bias and increase the validity of the findings. The random selection of schools within districts reduces selection bias. Comprehensive training of data collectors and the structured interview format aim at reducing participants’ reporting biases and at increasing the validity of responses. Allocation to intervention and control group at the cluster level performed by independent personnel following baseline assessment ensures that those collecting data are blind to the treatment conditions of the schools. While teachers’ reports of violence against students are a direct measure of behavioural change that considers the variety of daily interactions that teachers have with students, their reports could be influenced towards lower levels of violence by participation in the intervention. Students’ reports of violence by teachers therefore provide an additional valuable test of the intervention effect [42]. In addition, analyses will be carried out by an independent researcher not involved in field activities based on the groups as randomized (“intention to treat”) to minimize bias in statistical interpretation and reporting and to avoid incomplete accounting of participants and outcome events.

### Ethical considerations

As this research focuses on violence against children, ethical considerations and child protection are essential. The study has obtained ethics clearance from the Institutional Review Board and Ethics Committee of Shifa International Hospital (IRB # 040–23, approval date: April 28, 2023).

To protect participants’ identities, their data are pseudonymized through numeric codes. Participants’ data are stored only together with their individual code in a password-protected folder on a secure server. The document linking the numeric codes to individual participants is kept strictly confidential and separate from other data in a specific encrypted and password-protected file only accessible to selected members of the core research team. This also refers to video recordings of teachers participating in the intervention. Personal data are not disclosed to any other person without the participant’s permission or as required by the law. As behavioral intervention studies are minimum risk studies, no adverse events are expected as consequences of the intervention itself. However, the following may occur: first, questions about experiences of violence and mental health problems may evoke upsetting memories and feelings. Second, participants may present with severe mental health concerns, such as suicidal ideation or behaviour. Third, participants may experience severe ongoing abuse. In all cases, participants will receive immediate psychological support by a trained psychologist who is part of the research team. If necessary, appropriate referrals and follow-up for specialized services and further management are made on a case-by-case basis, with participant safety as the top priority. All adverse and unexpected events are documented by the research team.

### Data analyses

Analyses will be conducted using the statistical software *R* [69]. While an extensive evaluation of the psychometric properties of the study measures in the context of Pakistan is beyond the scope of this trial, we will examine internal consistency (through Cronbach’s Alpha) and criterion validity of the study measures (through bivariate correlations between theoretically related concepts) at each timepoint***.*** Baseline data will be used to examine the prevalence of maltreatment in different settings (across all study sites) as well as children’s mental health and well-being. The main analyses focus on testing the effects of the ICC-T intervention on primary (teacher-reported use of emotional and physical violence, student-reported experiences of physical and emotional violence), secondary (teachers’ attitudes towards violence, students’ mental health, well-being and cognitive functioning) and other outcomes (students’ academic performance and experiences of peer violence) at follow-up, with students and teachers as units of analysis. To test the effect of ICC-T over time, we will estimate linear mixed effects models including fixed effects of intervention group (ICC-T, control) and timepoint (baseline, follow-up 1, follow-up 2) and their interactions. Random effects for schools/school clusters and for participants (teachers, students) will account for the nested data structure and individual variability. Participant’ baseline score of the respective outcome and demographics (age and gender) will be included as covariates in the models. Missing data are only expected due to dropout at follow-up and handled through maximum likelihood estimation if the missing data are at least missing at random. This will be assumed if participants completing the follow-up assessments and those who are missing do not differ in primary outcomes and key demographic variables (age and gender) at baseline. Given the higher risk of type I errors associated with multiple outcomes, Holm-Bonferroni correction will be applied to primary outcomes and the false discovery rate (FDR) will be applied to secondary and other outcomes. Results will be presented including appropriate effect sizes and with a measure of precision (95% confidence intervals).

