### Study design

The study uses a two-arm multi-site cRCT design and is implemented in a total of 48 schools. Half of the schools are randomly allocated to the intervention group, which receives the ICC-T intervention, and the other half of schools to the control group, which receives no intervention. The study involves three data collection phases: baseline assessment directly before the intervention (t0), and two follow-up assessments approximately 6 months (t1) and 18 months (t2) after the intervention. Randomization of schools takes place after baseline assessment. See Fig. 1 for details.

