#### Sample size

The required sample size was calculated using the software *Optimal Design* [51]. Based on previous trials of ICC-T [37, 47], we expect moderate effects (δ = 0.25) for student-reported violence by teachers and large effects (δ = 0.35) for teacher-reported violence. In previous studies, the intra-class correlation was at 0.1 for teachers and 0.05 for students, and the covariance between baseline and follow-up scores of violence at the school level was around *r* = 0.30 [45, 46, 52]. We expect no drop out at the school level and an estimated attrition rate of 25% for students and 20% for teachers. Together with the specified parameters (α = 0.05; power = 0.80; effect size students: δ = 0.25, effect size teachers: δ = 0.35; ICC students = 0.05, ICC teacher = 0.01; R = 0.30) in total 48 schools with 27 students and 13 teachers per school are required to detect the expected intervention effects. The overall target sample is thus 1300 students and 720 teachers.

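### Read plainly, the mixed model assumes equal variance and equal correlation over 0, 6 and 18 months; if within-participant correlation fades, the 18-month standard error is about 5–15% too small

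*Protocol article*

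**What the plan says.** Study design sets a baseline and "two follow-up assessments approximately 6 months (t1) and 18 months (t2) after the intervention", so pairs of visits lie 6, 12 and 18 months apart. Data analyses specifies "linear mixed effects models including fixed effects of intervention group (ICC-T, control) and timepoint (baseline, follow-up 1, follow-up 2) and their interactions". On the random part it says "Random effects for schools/school clusters and for participants (teachers, students) will account for the nested data structure and individual variability". It adds that the "baseline score of the respective outcome and demographics (age and gender) will be included as covariates in the models". No random slope, visit-specific residual variance, residual correlation or school-by-time term is mentioned, and none is excluded. Missing follow-up data are to be handled by maximum likelihood.

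Sample size gives a school-level baseline/follow-up value of about 0.30 (called a covariance but written as r), attrition of 25% for students and 20% for teachers, and "In previous studies, the intra-class correlation was at 0.1 for teachers and 0.05 for students". The parameter list in the same paragraph has 0.01 for teachers. The protocol gives no correlation between visits for individual participants.

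**The concern.** Each participant has one score per visit, and timepoint is a factor. A participant intercept with independent residuals therefore makes all three pairs of visits equally correlated and all three visits equally variable. Neither is likely here. The primary scale refers to the past week, so scores 18 months apart will normally be less alike than scores 6 months apart. Violence is a sum score bounded at zero that the trial expects to fall, which tends to reduce its variance.

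Both group-by-time tests draw on one pooled residual variance. If correlation fades, the 18-month effect, the trial's only longer-term evidence, gets intervals that are too narrow. The Holm correction on the primary outcomes protects only if the p-values entering it are valid. With the expected attrition, likelihood estimation also relies on the covariance model; I have not put a size on that last effect.

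**Working it through.** **1. The plan's own figure.** Two-level cluster formula: variance = 4[ICC(1−R²) + (1−ICC)/n]/J, with J = 48, R² = 0.30² = 0.09, n after attrition, two-sided α = 0.05 (sidedness assumed), noncentral t with 46 df.
- Students: n = 27 × 0.75 = 20.25; variance = 4(0.0455 + 0.0469)/48 = 0.00770; SE 0.0878; power at δ = 0.25 is 0.796.
- Teachers: n = 13 × 0.80 = 10.4, ICC 0.10; variance = 4(0.0910 + 0.0865)/48 = 0.0148; SE 0.122; power at δ = 0.35 is 0.804.

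The planned power of 0.80 is reproduced with 0.30 read as a school-level correlation and the teacher ICC as 0.10. With 0.01 the teacher power would be 0.957.

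**2. Participant level, complete data, constant school effects.** The contrast is the difference between arms in mean change from baseline. Take total variance 1, participant share 1−ICC, N participants per arm, and participant-level (within-school) correlations r.
- True variance at visit k: (2/N) × 2(1−ICC)(1 − r(0,k))
- Variance under the intercept model, both visits: (2/N) × 2(1−ICC)(1 − r̄), where r̄ is the mean of the three correlations
- Ratio of model SE to true SE: √[(1 − r̄)/(1 − r(0,k))]

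Baseline score, age and gender are constant within a person, so with complete data they leave these contrasts unchanged. The correlations are assumptions; α comes from the normal distribution.

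| t0–t1/t1–t2/t0–t2 | 1 − r̄ | Ratio, 6 mo | α, 6 mo | Ratio, 18 mo | α, 18 mo |
|---|---|---|---|---|---|
| 0.4/0.4/0.3 | 0.633 | √(0.633/0.6) = 1.027 | 4.4% | √(0.633/0.7) = 0.951 | 6.2% |
| 0.5/0.5/0.3 | 0.567 | √(0.567/0.5) = 1.065 | 3.7% | √(0.567/0.7) = 0.900 | 7.8% |
| 0.6/0.6/0.3 | 0.500 | √(0.5/0.4) = 1.118 | 2.8% | √(0.5/0.7) = 0.845 | 9.8% |

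With equal correlations both ratios are 1. A simulation (48 schools, 20 students each, ICC 0.05, 6,000 runs) gave 4.2%/6.6%, 3.9%/8.2% and 2.8%/9.6% at 6/18 months. One literal fit with the baseline covariate included (0.5/0.5/0.3) gave a model SE of 0.0668 at both visits, against 0.0611 and 0.0741 estimated from the data.

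**3. School effects that change over time.** Students, 27 per school, N = 648 per arm, ICC 0.05, correlations 0.6/0.5/0.4.
- Constant school effects: true SE is √(0.003086 × 0.95 × 0.4 × 2) = 0.0484 at 6 months and, with 0.6 in place of 0.4, 0.0593 at 18 months. The model gives 0.0541 at both.
- School correlation 0.30: add (2/24) × 2 × 0.05 × 0.70 = 0.00583 to each true variance. True SEs become √(0.00235 + 0.00583) = 0.0904 and √(0.00352 + 0.00583) = 0.0967. The model gives 0.0560 at both, so the ratios are 0.62 and 0.58.

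Over four fading patterns (0.6/0.5/0.4, 0.5/0.4/0.3, 0.5/0.25/0.125, 0.7/0.49/0.343) with school correlation 0.30, the ratios are:

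| Group | 6 months | 18 months |
|---|---|---|
| Students, ICC 0.05 | 0.62–0.71 | 0.56–0.63 |
| Teachers, ICC 0.10 | 0.64–0.72 | 0.58–0.64 |
| Teachers, ICC 0.01 | 1.01–1.13 | 0.81–0.88 |

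**4. Attrition.** With students falling 27→24→20 per school (split assumed), 0.6/0.5/0.4 and constant school effects, the model SEs are 0.0561 and 0.0599 and the ratios 1.105 and 0.910. The SEs are no longer equal, but the directions stay.

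**5. Falling variance.** Take SDs of 1, 0.7 and 0.8 for the school and participant parts alike, school ranking preserved, 0.6/0.5/0.4. The true 6-month variance is 0.003086 × 0.95 × 0.65 + (2/24) × 0.05 × 0.3² = 0.00228, SE 0.0478. The model gives 0.0467 at both visits, now slightly too small at 6 months. At 18 months the true SE is 0.0557.

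**6. Baseline used twice.** With the baseline score as both outcome row and covariate, a covariate coefficient of 1 makes every baseline residual zero. If the baseline visit has its own variance, that variance can shrink towards zero and the likelihood rises without limit. On simulated data (48 × 20, school intercept kept) the log-likelihood, constant omitted, was −842 at a baseline SD of 1, 1,286 at 0.1, 3,387 at 0.01 and 7,587 at 0.0001. Each tenfold reduction below 0.1 adds about 48 × 19 × ln 10 = 2,100.

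**The case against.** The strongest objection is that the article does not say intercept. A participant intercept plus a random slope in months can be estimated from three visits even with timepoint as a factor. For the three patterns in step 2 (complete data, no school effect) it gives ratios of 0.99, 0.99 and 0.98 at 18 months and 0.99, 0.97 and 0.94 at 6 months. Covariance detail is also often left to an analysis plan, which is not shown here. This stands to the extent that a reader might infer the plan can only mean an intercept; the text does not support that. But it names the fixed effects, random effects and covariates and mentions no slope or visit-specific residual, so the intercept model is the plain reading and can be judged as such.

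Three other strong readings also fail. Equal standard errors at both follow-ups hold only with complete data (step 4). A 6-month standard error that is always too large, with lost power, needs stable school effects and variances; the protocol's own 0.30 reverses it for students, and for teachers at ICC 0.10 (step 3). And changing the participant covariance alone is not a sufficient repair: it leaves the school-level shortfall and fails while baseline is used twice (step 6).

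Finally, fading is assumed, and in the mildest case the 18-month type I error is only 6.2% (6.6% simulated). That stands, and it limits the size of the point.

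**Conclusion.** The point holds conditionally. If the participant effect is an intercept with independent residuals, and correlation fades within the assumed range, the 18-month standard error is about 5–15% too small. The 18-month direction was the same in every fading scenario examined under that model: constant or changing school effects, either teacher ICC, attrition and falling SDs. The 6-month overstatement of about 3–12% applies only with stable school effects and variances.

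With a school-level correlation of 0.30, the missing school-by-time variance is the larger problem for students, and for teachers at ICC 0.10. The sponsor should change the model; this does not undermine the design. The size rests on assumed participant-level correlations and on reading 0.30 as a correlation.

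**What to change.** In Data analyses:
- Replace the participant random intercept with an unstructured within-participant covariance over visits: a separate variance per visit and a separate correlation per pair of visits.
- Use baseline once. Either keep it as an outcome row and remove the baseline score from the covariates (3×3 covariance, group-by-time contrasts), or keep it as a covariate and model only the two follow-ups (2×2 covariance, arm effect at each visit).
- Keep the school random effect and add a school-by-time random effect.
- Fit by REML with small-sample degrees of freedom.

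The cost is a short rewrite and some R code, with no change to data collection. The 3×3 version has six within-participant covariance parameters instead of two, plus one school-by-time variance, which is little for a target sample of this size. The 18-month interval may widen. With school effects that change over time, both intervals will, because the narrower ones were not justified.
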